##### Qualitative semi-structured interviews

For the evaluation of the potential contextual factors (community/organisational level factors) that may influence implementation (barriers/facilitators) of the TERM framework (interviews/surveys), we will reach out to stakeholders and community groups within the participating municipalities using various communication channels: emails, face-to-face engagement at the site or during community events/other forums. Information about the study will be distributed and contact details will be provided for interested individuals.

Eligible participants will be invited to take part in qualitative interviews with a member of the research team. Participants will be given the option of being interviewed face-to-face (where feasible), via video-conferencing, or via telephone. Interviews will be audio-recorded using either handheld recorders or the video-conferencing software and transcribed verbatim by a professional transcription service. Using a semi-structured interview, participants will be asked a predefined series of open questions about the ENJOY IMP-ACT program, and also invited to expand on their answers through follow up questions and offer new topics of discussion.

### Intervention—implementation framework ‘TERM’

The implementation intervention is based on our previous piloted implementation framework [20] and includes several elements (‘TERM’, Figs. 1 and 4): **T**raining, **E**ngagement, **R**esources development, **M**arketing and promotion. This includes the core elements of the Interactive Systems Framework (ISF) and the ecologic framework [13, 29]. We identified the ‘TERM’ key elements as important mechanisms in building capacity, knowledge, upskilling and engagement, which thereby facilitate increased usage and uptake of physical activity using the Seniors Exercise Park. Evaluation of the implementation components and associated assessments’ timeline is detailed in Table 3.

**Fig. 4 Fig4:**
[figure not shown]
Proposed outlined of the activities to be carried out during the 9 months TERM intervention phase. Variation in the order of activities is expected between sites to accommodate council’s planning and seasonal weather

**Table 3 Tab3:** Evaluation of the implementation components using the RE-AIM dimensions and associated assessments’ timeline

	What will be measured (specific aim)	Tool/Measure	Assessment time-point^a^		
RE-AIM dimension			B1-B3	I1-I3	M1
Reach	The number of older people using the equipment (specific to aim 1a)	Modified SOPARC; Seniors Exercise Park observation form; My ENJOY Health usage	✓	✓	✓
	Number of exercise programs (aim 1b)	Audit of programs		✓	✓
Effectiveness	Physical activity level and health of users (aim 2a) Social return on investment (aim 3)	Face to face intercept survey: Self-reported physical activity, Quality of Life, social and health services	✓	✓	✓
Adoption	Number of allied health professional and organisations delivering programs (aim 1b)	Audit		✓	✓
	Number/type of seniors groups utilising the equipment (aim 1b)	Audit, Survey		✓	✓
	Number/type of exercise programs being delivered (aim 1b)	Audit, Survey		✓	✓
Implementation	Details and characteristics of programs being run (aim 1b)	Interview/Survey		✓	✓
	Older people’s usage characteristics of the equipment (e.g., frequency, duration) (2b)	Face to face intercept survey, Mobile app usage		✓	✓
Maintenance	Number of older people/programs/organisations using the equipment (aims 1a, 1b)	Modified SOPARC; Exercise Park observation form; Audit of programs; My ENJOY Health use			✓

^a^
*B1-B3* baseline, *I1-I3* during TERM implementation intervention, every 3 months, *M1* maintenance phase completion

#### ‘TERM’—Training – knowledge transfer

We aim to train allied health professionals and seniors champions, and to work closely with health-care and leisure centre providers in the areas surrounding the participating Seniors Exercise Parks, to support engagement during the trial and continuity beyond the study’s completion.
*Allied Health Professionals workshops*: A half-day workshop training program will be delivered at each site covering safe use, exercise prescription and program design, incorporating risk management, theoretical and practical sessions.
*Train the Trainer module (volunteer /champions)* – we will deliver a 5-week training module, 2 days per week (practical and educational components) to older people (based on successful seniors champions training utilised in our research [22]). We will train 6–8 leaders (ENJOY seniors champions) at each site, who will then be able to welcome and train community members on designated days (coordinated by the council). We will deliver 2 modules per site. Upskilling older people as champions can support and empower their peers to maintain participation in physical activity [30]. Using this approach maximises the engagement of the wider community with Seniors Exercise Parks.
*Induction sessions by qualified research staff (for example, accredited exercise physiologist or physiotherapist)* – 12 sessions will be offered at each site for extra support of park users who may require additional assistance or supervision, and further support for the volunteers (refresher sessions). For example, these sessions may support clients referred from local General Practitioner clinics or community health centres. This will enable transition of high-risk clients from supervised programs to the community with safe induction and familiarisation on the exercise equipment for future independent Seniors Exercise Park usage by these clients.

#### ‘TERM’—Engagement

Engagement with the community, older people, and stakeholders (local governments/health and leisure providers) is important for sustainability as well as effective design of scalable public health interventions [31]. Community engagement has been recognised as a pathway to building trust, encouraging participation, and promoting uptake [32]. We will engage communities through: (1) formal agreement sign-off (MOU with the participating councils), (2) local community events (e.g., open days, Seniors’ Weeks, Community Health Expos), (3) establishment of local advisory groups at each site, and (4) establishment of an overarching project advisory committee (Community of Practice committee). We will document progress in each of these steps as part of the process evaluation. The Community of Practice committee will include local and external stakeholder representatives (e.g., leisure centres, community health centres, council staff from various divisions (e.g., age and disability, community development, open space, leisure and recreation), ENJOY champions, community consumers) and state representatives (e.g., Municipal Association of Victoria, Sports Recreation Victoria, Department of Health).

#### ‘TERM’—Resource development

Our project resources will include information about the benefits of physical activity and safe usage of the equipment. These resources will comprise on-site information (instructional signage with friendly illustrations), traditional hard copy flyers, and an online platform/social media (website, video resources and the online mobile app, My ENJOY Health). We will also develop workshop and training resources (developed with a behaviour change focus), including on-line resources (video materials) and written educational materials (e.g., manuals).

*My ENJOY Health Innovative technology—*we have developed and tested a web mobile application that older people can access on-site via Quick Response (QR) codes fitted on the various exercise stations [22]. The QR codes link to instructions, safety tips, and 48 exercise videos. The existing web app will be upgraded as a native mobile application for iOS and Android (MY ENJOY Health). The platform will be further developed (co-design) to add (1) additional new sites, (2) additional features for engagement, (3) additional data extraction functionality and usage analysis.

#### ‘TERM’—Marketing and promotion

Effective marketing can support and motivate changes in behaviour or practice. Promoting physical activity therefore requires appropriate, relevant and well-resourced marketing to effectively create awareness and knowledge and increase older people’s motivation [33]. We will work closely with the marketing and promotion team within each council to reach older community members, using various targeted platforms: mail out flyers, on-site signage, newsletter stories, local radio stations, social media, and video promotions/photo shoots. As we anticipate variation in the marketing/promotion strategies between councils, we will develop a core strategy that is adaptable based on local structures and resources. This will include a social marketing approach, combining communications with supportive policies, environments and opportunities for physical activity [34].

### Assessments

#### Outcome measures

##### Primary outcomes

The primary impact measures of the implementation framework intervention are: (1) *the number of older people* who engage in physical activity using the Seniors Exercise Park (irrespective of usage mode: e.g., if via group-led programs or independent usage), and (2) *the physical activity level of users*.

Following the hybrid II design, we will evaluate the impact of the intervention and the potential contextual factors (community/organisational level factors) that may influence implementation (barriers/facilitators) of the TERM framework. In addition, we will evaluate older people’s quality of life, wellbeing and self-reported health care utilisation. The RE-AIM model [25] (see measures described in Table 3) and our logic model will guide the project evaluation (Fig. 1).

##### AIM 1a—Primary impact measure of the implementation intervention

The number of older people (users) engaging in physical activity using the Seniors Exercise Park will be evaluated using periodic observation (the System for Observing Play and Recreation in Communities (SOPARC)). The SOPARC is a reliable and feasible instrument for assessing physical activity and associated contextual data in community settings [35]. It is based on momentary time sampling techniques, which systematically and periodically scan individuals and contextual factors within pre-determined target areas in parks. We will use a modified version of the SOPARC, which will record number of visitors, the gender and activity modes/types of people utilising the Seniors Exercise Park [22]. Additional data about the type of usage of the equipment by coding the interaction with the outdoor exercise equipment (i.e., ‘using equipment as intended’ or ‘playing/looking/sitting’ on the equipment) will also be collected [22, 36]. Systematic scans will be conducted over a 10-day period (including weekend) with a total of 14 scans as follows: every 30 min of all park visitors in the study area during early morning (07:30–10:30), mid-day (12:00–13:30) and late afternoon (15:00–17:30) [37]. Evaluation will take place monthly during the control period (Baseline), every 3 months during the implementation intervention phase and once during the three-month maintenance phase. In the event that there are missing scans (e.g. due to days with extreme weather conditions), these scans will be rescheduled to an equivalent day.

##### AIM 2a –Physical activity level of older people users

We have already demonstrated that using the Seniors Exercise Parks improves physical function (objective measures), increases self-rated quality of life and wellbeing, reduces falls risk, and increases physical activity levels [17, 18]. ENJOY IMP-ACT aims to scale up this evidence-based program. We will conduct face-to-face intercept surveys with older people who utilise the equipment using the *self-reported physical activity* questionnaire from the Active Australia Survey (see below for more details) [38]. The survey assesses walking, moderate, and vigorous activity in the previous week, plus providing an indicator of total activity and meeting recommended physical activity guidelines. The Active Australia questions are valid, reliable and recommended for use in Australian population-based research. This will provide measures of time and frequency of physical activities and also identify any changes not likely to be attributable to the program (such as walking) [39], and provide a comparator to nationally representative data.

### Secondary measures

#### Intercept survey with park visitors

##### Users’ physical and health characteristics

Face-to-face intercept surveys (15–20 min) will be conducted at baseline (pre-implementation B1, B2, B3), during the implementation framework (I1, I2, I3), and at the end of the maintenance follow up (M1). Data will be collected during the periodic observation (SOPARC) days. Intercept surveys will provide more in-depth information about Seniors Exercise Park users’ characteristics. The paper-based survey will include a set of questions across various domains similar to previous research [37, 40], as well as validated questionnaires (detailed below). The set of questions will include socio-economic and demographic characteristics of Seniors Exercise Park users (e.g., age group, gender, country of birth, marital status), if they are local residents or visitors, motivation to use the Seniors Exercise Park equipment, how often they visit the park area, social connectedness/engagement with other people at the park area, their general physical activity level and their leisure/recreation activity at the park, and general health and wellbeing. Socio-economic status will be estimated using postcodes to derive the Australian Socio-Economic Indexes for Areas (SEIFA) 2021 Index of Relative Socio-economic Advantage and Disadvantage, where the first and tenth SEIFA decile represents geographical areas with the greatest socioeconomic disadvantage and advantage respectively [41]. Self-reported social and health-care services utilisation (e.g., General Practitioner visits, hospitalisations) for the 3 months prior, as well as leisure activities and occupation details, will also be collected at each time point to provide relevant information for the economic evaluation.

The following validated questionnaires will be used as part of the survey:
*Health-related quality of life* will be assessed using the EQ-5D-5L [42]. The EQ-5D-5L comprises five dimensions (mobility, self-care, usual activities, pain/discomfort and anxiety/depression), as well as an overall self-rated health status (Visual Analog Scale (VAS) 0–100) where a higher score represents better health. The utility score will be used for the economic evaluation.
*Self-reported physical activity* will be measured using the Active Australia Survey (Australian Institute of Health and Welfare, 2003 [38]). The Active Australia Survey includes six questions that assess walking, moderate and vigorous activity, in addition to an indicator of total activity. The Active Australia Survey questions were shown to be valid and reliable that can be used in Australian population-based research. The Active Australia Survey questions provide measures of time and frequency spent performing light, moderate and vigorous physical activities as well as an estimate of energy expenditure in metabolic equivalent (MET)-minutes per week.
*General wellbeing* will be assessed using the five-item World Health Organisation (WHO-5) Wellbeing questionnaire which provides measures of psychological wellbeing and depressive symptoms using 5 simple questions [43, 44]. A percentage score can be calculated using the raw score, which ranges from 0 (representing worst imaginable wellbeing) and 100 (representing best imaginable wellbeing).

##### Type of usage and uptake

We anticipate several ways in which older people will use the equipment: independent usage (e.g., incidental users), organised informal activities (e.g., seniors groups), and structured supervised programs delivered by community centre/leisure organisations. Audits of the number, type of programs (supervised/unsupervised), and program characteristics (duration, frequency, staff profession) will take place at the completion of the intervention via audit and/or survey from the service/program providers.

##### Online access monitor platform – the *My ENJOY Health*

We have developed an innovative online web application (*My ENJOY Health*) to monitor the usage and access of the Seniors Exercise Park by visitors at each site [22]. The online platform will be upgraded with additional features including programs, workouts, specific exercise instructions, videos, and safety tips. QR codes will be placed on the instructional signage and on the exercise equipment itself at each site. Visitors will be able to scan the QR code with their mobile phone at the site or download the native mobile application. The e-monitor tracker platform will collect information on usage of the online platform such as frequency, time, and date of access to the web/and or mobile app. Design and testing of the e-monitor tracker platform will be conducted in the first 3–6 months of the project.

##### Training audit and evaluation

Process evaluation of the training (allied health professional and train the trainer) will include: evaluation of the number/outcomes of workshops/training programs delivered for allied health professionals and seniors champions. A record of the participants will be kept (including their profession and qualification); and a structured evaluation of participants (knowledge gained, subsequent use of the Seniors Exercise Park with clients, and feedback) will be undertaken. Costs will also be collected for the allied health professionals and seniors champions training, as they form part of the investment, in the social return on investment analysis.

##### Contextual factors barriers/facilitators (Aim1c)—community/organisational level factors

To understand community level and organisational factors (e.g., funding, policy, internal structure) that may influence implementation (barriers/facilitators), we will conduct semi-structured interviews with key representatives from partner organisations (local government, and local healthcare /leisure/ recreation providers). In addition, we will conduct semi-structured interviews with leaders of delivery programs (seniors group leaders, allied health professionals, exercise instructors) using the outdoor equipment to understand provider characteristics, and barriers and facilitators experienced throughout their involvement with the Seniors Exercise Parks. The semi-structured interviews with stakeholder representatives and leaders of delivery programs will be conducted one-on-one via telephone, video conferencing or face-to-face. Semi-structured interviews will occur during the intervention and maintenance phases. The interviews will be audio-recorded or video-recorded. Audio-recording will then be transcribed by a professional transcription service.

##### Review and audit of physical activity programs

Information about the type and number of physical activity programs for older people using the Seniors Exercise Park will be provided by the council (from the Positive Ageing team or equivalent) to the research team. There may be different modes of delivery and or programs that will be delivered by the participating partners and/or their respective local health/leisure providers. This information will be collected in the last stage of each site, between 12 and 15 months.

##### Economic evaluation – social-return-on investment (SROI)

The information about the cost investment of participating councils will be collected via an online survey or a bespoke template that will be sent to the community of practice committee members (includes the six local government representatives for each Seniors Exercise Park) frequently at various stages during the trial. The following investment information will be collected and assigned a monetary value: capital costs (purchase, installation and setup); implementation costs (e.g., planning meetings, staff recruitment, marketing, communications, education to Australian Health Professionals and community leaders); running costs (e.g., health professionals, administration team, including the training costs for the allied health professionals and seniors champions) and maintenance costs (e.g., equipment maintenance). To complete the SROI analysis, the investment will be compared to the social return, which will include the monetary value of the Seniors Exercise Park via its impact on participant wellbeing, leisure and employment opportunity, and private and government funded social and health care utilisation (via data collected during the intercept interviews).

### Statistical methods

#### Sample size estimation and justification

##### A target outcome for successful Seniors Exercise Park usage

A NSW study demonstrated only 5.3% (*n* = 6) of older adults (> 60 years) utilise outdoor exercise equipment at a park [36]. In our field work we observed 10 older adults independently using the Seniors Exercise Park in a typical week following installation without any promotion or supported implementation. We anticipate that following the implementation intervention, there will be a 100% increase in the number of independent users (*n* = 20) as well as an increase in the number of older adults using the equipment as part of organised classes (*n* = 30) in a typical week (while accounting for weather impact [45]). Therefore, we would expect there will be approximately 50 equipment users observed over a 10-day period per site. This exceeds the reported fourfold usage increase following park refurbishment reported elsewhere [46]. Power calculations using a Poisson or negative binomial distribution, adjusting for site and weather differences [47] demonstrated that a power of over 0.95 can be achieved to detect a 100% increase in park visitors with this sample size.

##### Sample size calculation for the intercept surveys

Sample size calculations for the intercept surveys as part of aim 2 are based on the expected number of older people who will complete the survey using data from our previous project [22]. We observed 10 older people using the Seniors Exercise Park in a typical week (prior to formal promotion of the newly installed park). We hypothesised that the implementation intervention (TERM) will result in *at least* a twofold increase in the number of older people using equipment at the completion of the intervention phase (I3) compared to baseline (B1,B2,B3), with a 20% attrition rate (proportion of people refusing to be interviewed) during the maintenance phase (M1). Assuming 25% will decline to participate or have previously completed the survey [40], we will aim for a total of 54 intercept surveys (8 at baseline; 34 across I1-I3 and 12 at M1) per site, with an overall sample of 324 interviewees across the six sites. Each data collection period will include an observation period of 10 days (instead of a typical 7-day period as commonly used [35]). Increasing the number of observations days to 10 days will enhance opportunities for the research team to recruit more older visitors to complete the intercept surveys to meet the targeted sample size.

##### Sample size for the semi-structured interviews

For the stakeholder interviews (councils and community health/leisure centre), we aim to interview between 1–2 council staff from each council (5 councils so total of 5–10 interviews), and between 1–2 community health/leisure staff (6 park sites so total of 6–12 interviews). For the leaders of delivery programs (seniors group leaders, allied health professionals, exercise instructors), we aim to interview between 1–2 per site/park, hence a total of 6–12 interviews.

#### Statistical analysis

##### AIM 1—‘TERM’ implementation evaluation and impact

Descriptive statistics will be used to report the overall number of older people using exercise equipment as well as the type of usage and uptake, mobile app access, and survey responses from allied health professionals and seniors leaders. The proportion of missing data will also be reported descriptively, and if more than 10% of data are missing, data will be imputed using multiple imputation techniques. Generalised linear models [47] (with main effects for intervention, site, season and their interaction) will be used to examine the impact of the implementation intervention on the total number of older people (primary outcome) using the equipment with overdispersion handled using a negative binomial distribution. Sensitivity analyses will be undertaken by comparing models with missing data and imputed data.

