##### Intercept surveys

Each site will have a 3-month control period followed by a 9-month implementation intervention period (TERM—Training, Engagement, Resources development, Marketing and promotion), and a maintenance phase (3 months). Evaluation (observation of users/visitors and onsite intercept surveys) will take place each month during the control period (baseline = B), every 3 months during implementation intervention phase (I1, I2, I3), and once during the maintenance phase (M1), see Table 2 and Fig. 2. The control period will include three evaluation points (B1, B2, B3), each occurring over a 10-day period per month (including one weekend). The time series evaluation will enable controlling for variations in equipment access due to weather (seasonal effects). Potential participants (park users in the specified target area) will be approached by trained, clearly identifiable research staff to see if they meet inclusion criteria. They will be provided with a verbal explanation about the study and all ethical considerations and invited to participate in a survey. Interested participants will then be asked to provide a verbal agreement (consent) to participate. Upon verbal consent, a paper survey will be administered by the researcher onsite. If more than one person is in the park during any observation period, the research staff decision of who to approach would be guided by aiming to overall recruit an equal number of men and women. The participants will be eligible to complete only one intercept survey during the baseline and maintenance period. During the intervention period the same participants can be surveyed multiple times.

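### Scans that are never made up can read as low use: the Aim 1 total has no exposure term, and imputation starts only above 10% missing

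*Protocol article*

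**What the plan says.** Three parts of the protocol article bear on this.

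- **Observation schedule** (AIM 1a, primary impact measure): "Systematic scans will be conducted over a 10-day period (including weekend) with a total of 14 scans as follows". Half-hourly scans in a morning, a midday and an afternoon block are then listed. Scans missed for reasons such as extreme weather are covered without any threshold: "these scans will be rescheduled to an equivalent day".
- **Evaluation points** (Intercept surveys): "The control period will include three evaluation points (B1, B2, B3), each occurring over a 10-day period per month", then "every 3 months during implementation intervention phase (I1, I2, I3), and once during the maintenance phase (M1").
- **Analysis** (Statistical analysis, AIM 1): the terms are "Generalised linear models [47] (with main effects for intervention, site, season and their interaction"), and the model is for the effect "on the total number of older people (primary outcome) using the equipment with overdispersion handled using a negative binomial distribution". On missing data, "if more than 10% of data are missing, data will be imputed using multiple imputation techniques". A sensitivity analysis compares models with missing data against models with imputed data.

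No offset or other exposure term is named. The 10% is not tied to the whole dataset, a phase, a site or a window. The text does not say how an incomplete total enters the model when 10% or less is missing. The sample size section expresses the expected count as users per site over a 10-day period.

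**The concern.** A user can be counted only in a scan that takes place, so the exposure behind each count is the number of scans completed. If every window had its full set of scans, exposure would be constant and could be ignored. Rescheduling aims at that, but the Aim 1 analysis provides for missing data anyway, so the authors expect that some scans may not be made up.

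For those scans, a total with no exposure term treats a window with fewer scans like a complete one. Unrecovered loss in the control period inflates the apparent effect of the TERM intervention, and unrecovered loss in the intervention period hides part of a real one. The causes named in the article (weather, restrictions, site refurbishment) fall in particular months and so can fall in particular phases. This is one of the two primary outcomes.

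The stated amount of scanning per window is also unclear, and any exposure term would need that number.

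**Working it through.** **Inputs.** Six sites (Study design). Three baseline windows, three intervention windows and one maintenance window per site (Intercept surveys). That is 6 × 7 = 42 site-windows, of which 6 × 3 = 18 are baseline and 18 are I1–I3.

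**Step 1. The plan's own scan figure.** Scanning every 30 minutes:

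- 07:30–10:30 gives 6 scans, 12:00–13:30 gives 3 and 15:00–17:30 gives 5, if closing times are not scanned: 6 + 3 + 5 = 14.
- With closing times scanned: 7 + 4 + 6 = 17.

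So 14 is reproduced, but as one day's timetable, whereas the text gives it as the total over 10 days. If every slot were scanned on every day, a window would hold 14 × 10 = 140 scans. The article does not say that every slot is scanned daily, so 140 is an inference.

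**Step 2. Bias formula.** Let mB and mI be the shares of planned scans not made up in baseline and in I1–I3. Assume that lost scans add no users to the total, that use is otherwise similar across windows within a phase, and that loss is unrelated to use. Then

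observed ratio ÷ true ratio = (1 − mI) ÷ (1 − mB).

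**Step 3. Cases.**

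| Loss not made up | Share of all 42 site-windows | Factor on the usage ratio |
|---|---|---|
| One baseline site-window loses half its scans | 0.5/42 = 1.2% | 18/17.5 = 1.03 |
| 10% of baseline, none in I1–I3 | 1.8/42 = 4.3% | 1/0.90 = 1.11 |
| 10% of I1–I3, none in baseline | 1.8/42 = 4.3% | 0.90 |
| 10% in both phases | 3.6/42 = 8.6% | 0.90/0.90 = 1.00 |
| 9% of all scans, all in baseline | 9%; mB = 0.09 × 42/18 = 0.21 | 1/0.79 = 1.27 |
| 9% of all scans, all in I1–I3 | 9%; mI = 0.21 | 0.79 (a true doubling reads 2 × 0.79 = 1.58) |

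If the 10% is a share of the whole dataset, every row stays below the trigger.

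**Step 4. What an upward bias above 20% needs.** Setting 1/(1 − mB) = 1.20 gives mB = 16.7%, with nothing lost in I1–I3. At 10% lost overall across the 42 site-windows, about 85% of that loss would have to fall in baseline, with the rest in I1–I3: mB = 0.85 × 0.10 × 42/18 = 0.198, mI = 0.15 × 0.10 × 42/18 = 0.035, and 0.965/0.802 = 1.20. The 1.27 case means 0.21 × 180 = about 38 of the 180 baseline site-days (18 windows × 10 days) lost and never made up, with none lost later.

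**Step 5. With an offset.** If the expected count is a rate times the scans completed, the factor is 1.00 for any loss unrelated to use. If all scans are completed, the offset is constant, the intercept absorbs it and the result does not change.

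**The case against.** The strongest objection is that the plan already deals with lost scans. Each is to be rescheduled to an equivalent day, whatever the percentage, and Study setting and partners describes a contingency plan in the timeline for weather and refurbishment. Baseline windows take 10 days of each month, which leaves time to make scans up. This stands, and it limits the point to scans that could not be recovered. A reader might infer from the 10% rule that missing scans are acted on only above that level. The article does not support this: the threshold governs imputation only.

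Second, an article may leave an offset to the full analysis plan. That is fair, and an unnamed offset alone would not be a finding. Here, however, the article itself states the outcome as a total, the model terms and the imputation trigger, and that rule leaves incomplete totals at or below 10% unaddressed.

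Third, the article calls lost scans missing, not zero, and does not say that the rows are window totals. If individual scans were the rows, a lost scan would drop out without lowering a count. This also stands. The site-and-window reading rests on the outcome being called a total and on the sample size section counting users per site per 10-day period.

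Fourth, an offset is not free of assumptions. It treats lost scans as having the average use of their window. Scans lost to weather, or slots that would have held an organised class, may differ. That is why rescheduling should remain the first step.

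Staggered starts across sites also work against all loss falling in one phase, and season is in the model.

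**Conclusion.** The concern holds in a limited form. After rescheduling, scans not made up at or below an undefined 10% trigger can lower the modelled total and bias the usage ratio. The bias is about 3% for one half-lost baseline site-window and about 11% when one phase loses 10%. It is nil when loss is spread evenly.

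A reader might infer that the rule allows a bias above 20% as a matter of course. The documents do not support that. Such a bias needs rescheduling to fail on a large scale, the 10% to be a share of the whole dataset, lost scans to add nothing to the total, and nearly all loss to fall in one phase. If the 10% applies per phase, the most that one-phase loss can do is about 11%.

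Separately, the stated total of 14 scans over 10 days does not fit the listed timetable, which gives 14 (or 17) in one day. This is an inconsistency to reconcile and does not itself show bias.

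**What to change.** - **Model.** In the Aim 1 negative binomial model, analyse the count per site and evaluation window with offset log(scans completed in that window), whatever the percentage missing.
- **Missing scans.** Keep rescheduling to an equivalent day as the first step. Keep multiple imputation as a sensitivity analysis. If the 10% rule is retained for any purpose, state the unit to which it applies.
- **Schedule.** Reconcile the scan total with the timetable in the AIM 1a section. The sponsor should confirm and state the number of scans per day and per 10-day window, and whether closing times are scanned.

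The cost is one model term and a clarified schedule. The only record needed is which scans were completed, so no extra field observation is required. The small downside is the assumption that lost scans had average use for their window.
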